#### Exploratory analysis on the primary outcome

If a statistically significant result is observed for the primary outcome a parsimonious statistical model describing the predictive value of variables listed will be estimated, using a stepwise model building procedure (Additional file 2 Appendix 1). The linearity in response of continuous variables will be examined using restricted cubic splines. Interaction terms will be assessed and Akaike's Information Criterion will be used to determine the best model fit [21].

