### Primary outcome measure

The primary outcome is Surgical Site Infection (SSI) within 30 days of surgery.

Positive identification of SSI will be determined with use of the internationally accredited Centers for disease Control and Prevention (CDC) definitions.

We hypothesise that the use of wound-edge protection device in adults undergoing laparotomy will result in a reduced rate of surgical site infection of 50% based on evidence from Horiuchi et al, 2007 [12].

The power calculations for a range of baseline infection rates and this assumed 50% reduction in SSI rate brought about by use of the device are shown in table 2.

**Table 2 T2:** Infection rates and sample size

Infection rate in untreated group	Expected infection rate in treated group	Overall sample size	Sample size in each arm
18%	9%	448	224

15%	7.5%	554	277

12%	6%	**710**	**355**

(80% power and 0.05 significance level)

A conservative estimate of infection rate of 12% requires a total of 710 patients, randomised 1:1 between treatment and placebo. Thus we intend to recruit 750 patients in total in order to provide adequate power should our assumptions informing the power calculation prove optimistic, and to accommodate a potential 5% dropout rate.

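### Stepwise/AIC selection on about 64 expected infections is likely to make the exploratory SSI model optimistic; whether it also names false predictors depends on a candidate list and stepping rule not shown

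*Protocol article*

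**What the plan says.** The protocol article, section *Exploratory analysis on the primary outcome*, makes this model conditional on a significant primary result. The procedure is then fixed: "a parsimonious statistical model describing the predictive value of variables listed will be estimated, using a stepwise model building procedure". The variables are listed in Appendix 1 of Additional file 2, which is not shown. Restricted cubic splines serve to check linearity of continuous variables. The section ends: "Interaction terms will be assessed and Akaike's Information Criterion will be used to determine the best model fit".

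The section *Primary outcome measure* supplies the figures that determine the event count: "A conservative estimate of infection rate of 12% requires a total of 710 patients", at "80% power and 0.05 significance level", with an assumed halving of the SSI rate. It adds "Thus we intend to recruit 750 patients in total", partly "to accommodate a potential 5% dropout rate".

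Three other places bear on the point:
- *Statistical analysis* makes every p value except the primary one nominal.
- *Analysis of Primary and Secondary Outcomes* puts surgeon in the primary model as a random effect.
- *Secondary Outcomes*, items 1 and 2, and the Abstract ask how contamination and comorbidity affect the device's efficacy; the Abstract adds operative characteristics.

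**The concern.** The model's stated purpose is to describe how well variables predict SSI. Data-driven selection distorts that quantity when events are few: terms are kept partly because their estimates happened to be large in this sample, and the same data are then used to judge the fit. Coefficients and apparent discrimination come out too favourable. Labelling the p values nominal does not correct this.

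The interactions matter most. The exploratory section is the only place in the article that mentions interaction terms, while the effect of the device by contamination and comorbidity is a declared secondary question. An interaction kept by chance could be read as saying which patients benefit.

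**Working it through.** **1. The plan's own sample size.** Pooled-variance formula for two proportions, two-sided 0.05, power 80%, 12% vs 6%, mean rate 0.09:

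n = [1.960 × √(2 × 0.09 × 0.91) + 0.842 × √(0.12 × 0.88 + 0.06 × 0.94)]² / 0.06² ≈ 356 per arm.

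The article gives 355, for which power is 79.9%. The other rows give 278 and 226 against the stated 277 and 224. The table is reproduced.

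**2. Expected infections.**
- N=710: 355 × 0.12 + 355 × 0.06 = 42.6 + 21.3 = 63.9.
- N=712 (750 less 5%): 356 × 0.18 = 64.1.
- N=750, 12% row: 375 × 0.18 = 67.5.
- N=750, 15% row: 375 × 0.225 = 84.4.
- N=750, 18% row: 375 × 0.27 = 101.3.

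**3. Optimism at about 64 events.** The candidate list is not shown, so candidate sets, prevalences and effects below are assumptions. Each trial was simulated at 12% vs 6% SSI, a logistic model was selected stepwise, and it was then applied to new patients.

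| Assumed candidates | Rule | AUC, trial data | AUC, new data | Calibration slope |
|---|---|---|---|---|
| Contamination (3 df), diabetes, obesity, smoking, and their 6 device interactions; N=712 | AIC | 0.70 | 0.64 | 0.65 |
| same | p<0.05 | 0.68 | 0.63 | 0.67 |
| 10 generic, 3 true; N=710 | AIC | 0.73 | 0.69 | 0.80 |
| 15 generic, 3 true; N=710 | AIC | 0.74 | 0.68 | 0.73 |
| 20 generic, 4 true; N=710 | AIC | 0.76 | 0.70 | 0.72 |

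The first set with device itself is 13 df, so 63.9 / 13 = 4.9 events per df. Under AIC the AUC is too high by about 0.04 to 0.06. With p<0.05 stepping on the generic sets the gap is 0.03 to 0.05 and the slope 0.78 to 0.84, so the optimism does not depend on AIC alone.

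These runs were not restricted to trials with a significant device effect. A separate simulation that was (712 patients, 10 or 15 candidates, 3 true) gave AUC 0.74 to 0.76 in the trial data against 0.68 to 0.69 in new patients, so the restriction does not remove the gap.

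**4. False terms.** AIC keeps a null one-df term when its chi-square exceeds 2: P = 0.157. For m independent noise terms, P(at least one kept) = 1 − (1 − a)^m.

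| Noise terms | AIC, a = 0.157 | p<0.05, a = 0.05 |
|---|---|---|
| 4 | 0.50 | 0.19 |
| 5 | 0.58 | 0.23 |
| 10 | 0.82 | 0.40 |
| 13 | 0.89 | 0.49 |
| 14 | 0.91 | 0.51 |
| 15 | 0.92 | 0.54 |

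The simulations agree. In the generic sets, with 7, 12 and 16 noise terms, AIC kept at least one in 69%, 86% and 93% of runs. In the first set, where all six interactions are null, AIC kept a false one in 69% of runs and p<0.05 stepping in 33%.

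**5. Which problem comes from the event count.** Repeating the first set under AIC with 2800 patients, about four times as many, moved the false-interaction rate only from 69% to 66%. The optimism shrank clearly: AUC 0.69 vs 0.67, slope 0.90. Few events cause the optimism; the criterion and the number of candidates cause the false terms.

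**The case against.** The strongest reply is that this is a labelled exploratory analysis with nominal p values, described in a condensed article, and that stepping levels, shrinkage and validation may be set out in Additional file 2, the full protocol or the SAP. That stands: the article's silence on validation is not counted here. What remains is the method it does fix, a stepwise search with AIC and interactions.

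Some stronger readings are tempting but not supported:
- **That the model will usually name false predictors because there are only 64 infections.** The false-term rate hardly depends on the event count. It depends on the candidate list and on whether AIC governs every step or only compares finished models, which the text leaves open. With p<0.05 stepping and 10 noise terms the chance is about 40%.
- **That splines enlarge the search.** They are stated as a check of linearity and add flexibility only if that check changes the model. No spline terms were simulated.
- **That 64 is the expected count whatever happens.** It comes from the lowest, deliberately conservative row of Table 2. Higher SSI rates would ease the optimism.
- **That a clinical risk score is promised.** The article speaks only of describing the predictive value of variables.

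**Conclusion.** The concern holds as a minor point. If the control rate is near 12% and the device halves it, the selected model rests on about 64 infections and is likely to be optimistic: AUC too high by about 0.04 to 0.06 and a calibration slope of about 0.65 to 0.80 under AIC and the assumed candidate sets. At the 15% or 18% rate, with about 84 or 101 events at N=750, the optimism should be smaller; those cases were not simulated.

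False terms are a separate and conditional risk. At least one is more likely than not from 5 noise candidates under AIC, but only from 14 under p<0.05 stepping.

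The simulations assume covariate prevalences and effects and leave out the surgeon effect, so their figures show scale rather than predict the trial. The primary comparison does not use this model and its conclusion is unaffected.

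**What to change.** In *Exploratory analysis on the primary outcome*, replace the stepwise/AIC search with one model fixed in advance, containing:
- device and contamination class;
- a short list of the named comorbidity and operative variables;
- the device-by-contamination and device-by-comorbidity interactions that match secondary outcomes 1 and 2;
- surgeon as a random effect, as in the primary analysis.

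Fit it with penalisation, because even a short list with these interactions leaves only about 5 events per df at the sizing assumption. Report every term, and give bootstrap optimism-corrected discrimination and calibration.

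If selection is retained, repeat the whole selection procedure, including the choice of interactions, in each bootstrap sample, and report the corrected values beside the apparent ones.

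Cost: a wording change and modest programming, with no new data. The model will be less short and its apparent fit less favourable.

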#### Cost-effectiveness Analysis

A prospective within trial cost-effectiveness analysis will be undertaken based on ITT analysis of all patients enrolled in the study. The incremental cost per quality adjusted life year (QALY) gained and incremental cost per life year gained of the alternate treatment options will be assessed during the trial to inform clinicians and policy makers of the cost effectiveness of the alternative therapies.

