## Background

Surgical site infection (SSI) is one of the most common postoperative complications and occurs in at least five percent of all patients undergoing surgery [1]. The rate of SSI is significantly higher after open abdominal surgery which can carry an SSI risk of up to 40% depending on the level of contamination [2].

SSI is associated with considerable morbidity and it has been reported that over one-third of postoperative deaths are related, at least in part, to SSI [3]. It must be appreciated, however, that the diagnosis covers a wide spectrum of clinical conditions ranging from a relatively trivial wound discharge with no other complications to a life-threatening condition. Other clinical outcomes of SSI include poor scars that are cosmetically unacceptable, such as those that are hypertrophic or keloid, persistent pain and itching and a significant impact on emotional wellbeing [4].

SSI can double the length of time a patient stays in hospital and thereby increase the costs of health care. Additional costs attributable to SSI of between £814 and £6626 per case have been reported depending on the type of surgery and the severity of the infection [5,6]. The main additional costs are related to re-operation, extra nursing care and interventions, and drug treatment costs. The indirect costs, due to loss of productivity, patient dissatisfaction and litigation, and reduced quality of life, have been studied less extensively.

Recent national guidelines concerning the prevention and treatment of SSI have been issued by the National Institute for Health and Clinical excellence (NICE) [7]. These recommendations are based on systematic reviews of best available evidence, or when minimal evidence is available the guideline development group's opinion of what constitutes good practice. Intra-operative guidance includes the role of hand decontamination, sterile gowns and drapes and antiseptic skin preparation. Wound-edge protection devices are not discussed in these guidelines, presumably due to the paucity of published research into their use and efficacy in the prevention of infection

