### Secondary Outcomes

Comparisons will be made to assess the impact of treatment relating to the following outcomes:

1) The degree of wound contamination (e.g. colorectal resections/vascular surgery)

2) Presence of major comorbidity (e.g. diabetes, obesity, smoking)

3) Health-related quality of life (QoL) to be assessed using the EQ-5D questionnaire

4) Length of stay in hospital

5) Health care utilisation and the incremental cost-effectiveness of the use of the wound-edge protection device compared to standard care

6) Adverse events

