### Trial Management Protocols

Two named principle investigators (PI) will be recruited at each study site. Together they shall provide blinded wound reviews for the other PI's patients by being unaware of which arm of the study these patients belong to. The two wound reviews will occur firstly prior to discharge at day 5 to 7 post-operation and then a formal outpatient appointment or ward attendance for wound review will be arranged at or just after 30 days (day 30-33 post-operation). At this visit patients will also be asked to complete a retrospective questionnaire regarding their wound and its healing over the intervening period. This will ensure that full information is gathered about any wound infections, together with resulting treatment or hospital admissions, occurring between the day 5-7 and day 30-33 reviews. Enrolled patients will also be given contact details for the local primary investigator should any concerns by raised by the patient. Wound assessment at both stages will utilise a standardised proforma. These wound assessment tools will be pre-validated for reproducibility and ease-of-use in a pilot study to be ran prior to full trial launch.

QOL data will be assessed using the EQ-5D pre-operatively, at 5-7 days, at the 30-33 day follow-up visit.

We also envisage the involvement of clinical nurse specialists at most sites. Their clinic appointments are generally more accessible and it may be feasible to utilise these for the second formal (outpatient) wound review. Clinical nurse specialists are generally experienced in assessing post-operative wounds themselves and they may also therefore provide a second-line cohort of blinded wound reviewers if the relevant PI is not available.

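### Cost per life year gained is planned within a trial whose follow-up ends at day 30-33; the ratio can be computed but would be uninformative

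*Protocol article*

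**What the plan says.** The Cost-effectiveness Analysis section of the protocol article sets the frame: "A prospective within trial cost-effectiveness analysis will be undertaken based on ITT analysis of all patients enrolled in the study". It then names two ratios. One is the "incremental cost per quality adjusted life year (QALY) gained"; the other is the "incremental cost per life year gained of the alternate treatment options". The section says the results are meant for clinicians and policy makers.

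The time frame is given elsewhere. Under Trial Management Protocols, the second and last wound review is at day 30-33, and the utility data follow the same schedule: "QOL data will be assessed using the EQ-5D pre-operatively, at 5-7 days, at the 30-33 day follow-up visit". The Abstract says resource use is also captured. No later contact, survival follow-up, mortality outcome or extrapolation model is described.

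Under Primary outcome measure: "The primary outcome is Surgical Site Infection (SSI) within 30 days of surgery". The economic item under Secondary Outcomes names no unit of effect: "Health care utilisation and the incremental cost-effectiveness of the use of the wound-edge protection device compared to standard care".

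**The concern.** A life-year ratio needs a difference in survival time as its denominator. In a within-trial analysis that stops at about one month, survival time is cut off at 33 days. Only deaths inside that window count, and each averted death is credited only with the days left until the window closes. The denominator is therefore very small and depends on few events.

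When a ratio's denominator cannot be told apart from zero, its size and sign are largely a matter of chance and its confidence interval may be unbounded. Cost-effectiveness is a named secondary outcome with a policy audience. A ratio named in advance is expected to be reported, and readers usually take cost per life year to cover the life gained after an averted death. Here nearly all of that life would be left out.

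**Working it through.** **The plan's own figure.** The article gives no figure for the economic analysis. The only computed figure that bears on this point is the sample size for SSI of 12% v 6% (80% power, 0.05 significance, taken as two-sided): 355 per arm. The usual two-proportion formula gives 356 with pooled variance and 354 with unpooled variance, so the figure reproduces. Allowing 5% dropout, 710/0.95 = 747.4, rounded up to 748, so 750 covers it. I use 750/2 = 375 per arm below.

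**Cap on life years.** 30/365.25 = 0.082 and 33/365.25 = 0.090 life years per patient.

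**Credit per averted death.** If deaths are spread evenly over 33 days, the mean loss per death is 33/2 = 16.5 days (15 days for a 30-day window).

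**Between-arm difference.** The article gives no mortality rate, so control mortality m is assumed at 1% to 10%. Two effects on mortality are tried:
- *One-sixth fewer deaths.* The Background says that more than a third of postoperative deaths are related at least partly to SSI. Take one third, and let the hoped-for halving of SSI halve those deaths: 1/3 x 1/2 = 1/6.
- *Half of all deaths prevented.* This is the extreme case in which every death is tied to SSI.

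Days lost per patient have mean 16.5m and variance m x 33²/3 - (16.5m)² = 363m - (16.5m)². The gain is 16.5 x (m_control - m_device). The standard error is the square root of (variance_control + variance_device)/375.

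| Control mortality (assumed) | Deaths reduced by | Gain, days | SE, days | Gain/SE |
|---|---|---|---|---|
| 1% | 1/6 | 0.028 | 0.133 | 0.21 |
| 3% | 1/6 | 0.083 | 0.228 | 0.36 |
| 5% | 1/6 | 0.138 | 0.293 | 0.47 |
| 10% | 1/6 | 0.275 | 0.406 | 0.68 |
| 1% | 1/2 | 0.083 | 0.120 | 0.69 |
| 3% | 1/2 | 0.248 | 0.207 | 1.20 |
| 5% | 1/2 | 0.413 | 0.265 | 1.56 |
| 8% | 1/2 | 0.660 | 0.332 | 1.99 |
| 10% | 1/2 | 0.825 | 0.369 | 2.24 |

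In years, the gains run from 0.0275/365.25 = 0.00008 to 0.825/365.25 = 0.0023. At 5% mortality with deaths halved, an estimate equal to the expected gain would have a 95% interval of 0.4125 ± 1.96 x 0.2652, or -0.11 to 0.93 days. The gain reaches about two standard errors only when mortality of 8% to 10% is combined with a halving of all deaths.

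**The alternative denominator.** At the planning rates, SSIs avoided per patient are 0.12 - 0.06 = 0.06. The SE is the square root of (0.12 x 0.88 + 0.06 x 0.94)/375 = the square root of 0.162/375 = 0.0208. The 95% interval is 0.019 to 0.101 and the ratio to the SE is 2.9. This is the difference the trial was sized to detect.

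**The case against.** Four points can be made on the other side.

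*The ratio is estimable.* A life-year difference restricted to 33 days can be calculated, so it would be wrong to say that the ratio cannot be estimated. This stands. The fault is that the result carries almost no information and discards nearly all the life gained from an averted death.

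*Cost per QALY has the same horizon.* It is also capped at 0.09 per patient. If an SSI cost an assumed 0.1 to 0.3 of utility for the full 33 days, the QALY gain would be 0.06 x 0.1 x 33/365.25 = 0.0005 to 0.0016 per patient, which is just as small. That is why net benefit is the better way to show its uncertainty. But EQ-5D can register the effect of a non-fatal infection, which a life-year count cannot, and the QALY keeps results comparable across disease areas. It is worth keeping.

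*The article is condensed.* A reader might infer that leaving out cost per SSI avoided is itself an error. The document does not support that: the secondary outcome names no effect unit, and a fuller protocol or economics plan could include the measure. The point rests on what the article states, not on what it omits.

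*The replacement can also be misread.* A reader might want to set a net cost per SSI avoided against the Background figures: "Additional costs attributable to SSI of between £814 and £6626 per case have been reported". That would count the saving twice, because the net cost already has those costs subtracted. At 0.06 SSIs avoided, the averted cost is 0.06 x £814 = £49 to 0.06 x £6626 = £398 per patient. If the device adds less cost than is averted, it is both cheaper and more effective, and a ratio should not be quoted. No cost-per-life-year figure in pounds is offered here, because the article gives neither a net cost nor a mortality rate.

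**Conclusion.** The point holds in this limited form. The stated life-year ratio does not fit a within-trial analysis with follow-up to day 30-33. For assumed 30-day mortality of 1% to 5%, its denominator is between 0.03 and 0.41 days per patient and between 0.2 and 1.6 standard errors from zero. Crediting the article's own link between SSI and death at one third leaves it below 0.7 standard errors even at 10% mortality.

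The conclusion rests on three things: the within-trial wording excludes extrapolation; deaths are spread evenly over the window; and the assumed mortality range is reasonable. It weakens only if mortality is about 8% or more and the device halves all deaths. Even then the truncation at 33 days remains.

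The weight is moderate. One of two named economic ratios would be uninformative. The primary analysis, the sample size and the cost-per-QALY analysis are not called into question.

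**What to change.** In the Cost-effectiveness Analysis section, replace incremental cost per life year gained with incremental cost per SSI avoided within 30 days, based on the primary outcome and the resource-use data. Keep cost per QALY, with uncertainty preferably shown as incremental net benefit so that a near-zero QALY difference does not break the summary. State that dominance will be reported instead of a ratio if the device proves both cheaper and more effective. Do not benchmark a net cost per SSI avoided against the quoted attributable cost per case.

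The core change is one sentence and needs no new data, since SSI, resource use and EQ-5D are already collected. The small drawback is that cost per SSI avoided cannot be compared across disease areas; the retained QALY analysis covers that.

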### Data Safety Monitoring

A steering committee developed the protocol and will provide academic leadership for the overall conduct of the trial. An independent data and safety monitoring board will be appointed who will undertake 4 interim analyses on safety and efficacy. Although the exact details of the statistical plan will be determined by the committee, it is anticipated that a truncated modified O'Brien Flemming alpha spending plan will be used for efficacy, and a non symmetrical power function will be used for safety (increasing the likelihood of early stopping for safety).

